### Trial design

The TURN-OUT trial is designed as a superiority, double blind, multicentre, randomised, controlled clinical trial with two parallel groups and a primary endpoint of fetal mode of delivery at birth. Randomization will be performed as block randomization with a 1:1 allocation.

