### Sample size

The sample size (416) was calculated on the basis of the primary outcome. This power calculation is based on our prospective cohort of women with a fetus in the OT position [3], and our surveys of obstetricians and midwives who would perform a manual rotation if it reduced the rate of operative delivery by about 18% [10, 11]. To detect a reduction in operative delivery from 49% in controls to 35% in the intervention group, a sample size of 208 in each group (total = 416) will be required for α = 0.05 (two-tailed), β = 0.20 (power = 80%) (calculated using Epi Info™ version 3.3.2, Centers for Disease Control and Prevention, Atlanta, USA).

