#### Analysis

Analysis will be on an intention-to-treat basis (according to treatment allocation), including withdrawals and losses to follow-up. Losses to follow-up for the primary outcome are not expected because randomisation will occur at full dilatation and the primary outcome is the mode of delivery. The results will be reported according to the Consolidated Standards for Reporting Trials (CONSORT) guidelines.

Demographics and other potential confounders will be compared by treatment allocation in a univariate analysis. Categorical outcome measures will be compared by proportions (chi-squared test), means for normally distributed data (t-test) or rank order for non-normally distributed data (Mann-Whitney U test).

A logistic regression analysis of treatment allocation and other variables on the primary outcome measure, operative delivery, will be performed. The following variables will be considered for the logistic regression model: maternal body mass index, maternal age, maternal height, maternal ethnicity, gestation, induction of labour, gestational diabetes, neonatal gender and RCOG CTG classification in the second stage of labour. Parity, study site and the presence of epidural for intrapartum analgesia at the time of randomisation will not be included because randomisation is stratified for these variables. Only variables where *P* <0.25 in the univariate regression will be included in the multivariate model. Continuous variables that do not show a linear association with the logit function will be divided into quartiles and treated as categorical. Interaction terms will be considered for treatment allocation versus each of the other variables and, where clinically appropriate, between non-treatment variables. *P* <0.01 will be considered evidence of interaction. Terms will be excluded from the model in a stepwise backward manner until all remaining terms are both statistically significant (*P* <0.05) and clinically significant (that is, removal of the term results in a clinically significant change in the estimate of the odds ratio of treatment allocation for the primary outcome). The analysis will be performed using SAS 9.2 (or a more recent version of SAS, Statistical Analysis Software. Cary, USA).

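### The supplementary adjusted model for operative delivery is chosen from the trial data, partly by how far each covariate moves the treatment odds ratio; it should be one pre-specified model

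*Protocol article*

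**What the plan says.** The Abstract makes the chi-squared test the comparison for the primary outcome and adds a logistic regression to deal with possible confounders. The Analysis section of the Protocol article fixes how that regression is built:

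- **Candidates.** Nine variables are listed: body mass index, age, height, ethnicity, gestation, induction, gestational diabetes, neonatal gender and second-stage CTG class. None is forced in.
- **Screen.** Only those with univariate P<0.25 enter the multivariable model.
- **Functional form.** Continuous variables that are not linear on the logit scale "will be divided into quartiles and treated as categorical".
- **Interactions.** "Interaction terms will be considered for treatment allocation versus each of the other variables", and between other variables where clinically sensible. The criterion is P<0.01.
- **Removal.** "Terms will be excluded from the model in a stepwise backward manner until all remaining terms are both statistically significant" (P<0.05) and clinically significant. The second condition is defined as follows: "removal of the term results in a clinically significant change in the estimate of the odds ratio of treatment allocation". No number is attached to it.
- **Stratification factors.** Parity, site and epidural are kept out because randomisation was stratified on them. The section on randomisation gives the reason for stratifying: their association with operative delivery may be strong.

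**The concern.** This is a rule for finding confounders in observational data. With "block randomization with a 1:1 allocation", any difference between arms in a baseline covariate is due to chance. A covariate earns its place in a trial model because it predicts the outcome. The removal rule adds a second test, movement of the treatment OR. A prognostic covariate passes that test mainly when it happens to be imbalanced, and partly because the OR is non-collapsible. A strong predictor that is well balanced fails and is removed. The factors the protocol itself rates as likely strong predictors never enter.

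Three things are at stake, all concerning the adjusted result:

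- Which covariates remain is decided by looking at the treatment estimate, against a threshold nobody has written down.
- The standard error (SE) and confidence interval treat the final model as if it had been fixed in advance.
- If a treatment interaction is kept, the treatment coefficient is the effect at one covariate level and no longer an overall effect.

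**Working it through.** **1. Reproduce the design figure.** Inputs from Sample size: "To detect a reduction in operative delivery from 49% in controls to 35% in the intervention group", two-sided alpha 0.05, power 80%, and "a sample size of 208 in each group (total = 416) will be required".

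n = [1.960·√(2·0.42·0.58) + 0.842·√(0.49·0.51 + 0.35·0.65)]² / 0.14² = 193.9, or 194 per arm.

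With continuity correction: (193.9/4)·[1 + √(1 + 4/(193.9·0.14))]² = 207.96, or 208 per arm and 416 in total. The stated figure is reproduced. It rests on the unadjusted comparison, so nothing below changes it. The design OR is (0.35/0.65)/(0.49/0.51) = 0.56.

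**2. The entry screen.** If all nine candidates were pure noise, 9 × 0.25 = 2.25 would be expected to pass, and the chance that at least one passes is 1 − 0.75⁹ = 0.92.

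**3. Why retention follows imbalance.** Suppose there is no treatment effect and a covariate has log-OR b per SD. Dropping it moves the treatment log-OR by roughly b × d, where d is the chance difference in covariate means. With 208 per arm, d has standard error √(2/208) = 0.098 SD. For b = 0.5 and an assumed 5% threshold, d must exceed ln(1.05)/0.5 = 0.098 SD, about one standard error. That happens in about 32% of trials. At 10%, d must exceed ln(1.10)/0.5 = 0.191 SD, or 1.94 standard errors, about 5% of trials. So a clearly prognostic covariate is kept or dropped largely according to the luck of the allocation.

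**4. Simulation of the rule.** Assumptions, none of them in the protocol: nine independent standard-normal covariates with log-ORs per SD of 0.8, 0.5, 0.5, 0.3 and five zeros; N = 416; 1,500 trials per setting; treatment forced in; interactions not carried into the selected model. The comparator is a fixed model with all nine covariates. A strong predictor is one with log-OR of at least 0.5. The first three result columns give no effect / conditional OR 0.56 where two figures are shown.

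| Assumed OR-change threshold | Strong predictors kept | No covariate left | Type I error | Median OR at design effect | Significance differs from fixed model, design effect | Power, rule vs fixed |
|---|---|---|---|---|---|---|
| 2% | 69% / 74% | 2% / 1% | 0.057 | 0.56 | 4% | 0.748 vs 0.731 |
| 5% | 31% / 44% | 32% / 20% | 0.062 | 0.57 | 7% | 0.753 vs 0.743 |
| 10% | 7% / 15% | 82% / 63% | 0.051 | 0.60 | 10% | 0.709 vs 0.725 |

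Median ORs for comparison were 0.55-0.56 for the fixed model and 0.63-0.64 unadjusted. As the threshold rises, the adjusted OR drifts from the conditional towards the unadjusted value, so what it estimates depends on the unstated number.

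Under no effect at the 5% threshold, the rule's mean SE was 0.206 against an empirical SD of 0.219, a ratio of 0.206/0.219 = 0.94. The fixed model gave 0.225 against 0.230. Monte Carlo error is about √(0.05·0.95/1500) = 0.006 on type I error and 0.219/√3000 = 0.004 on the SD.

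A second simulation, with nine covariates of OR roughly 1.2-2 and 49% vs 35%, gave power of 0.870 (rule) vs 0.869 (fixed) at 5%, and 0.830 vs 0.861 at 10%.

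**5. Interactions.** Nine treatment interactions at P<0.01, taken as independent, give 1 − 0.99⁹ = 0.086. The two simulations gave 7.3-9.7% and 5-7%. If all 36 covariate pairs were searched as well (45 terms), the figure would be 1 − 0.99⁴⁵ = 0.36. That is an upper case, because the protocol limits those pairs to clinically sensible ones.

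**The case against.** The best defence is that this model is supplementary. The chi-squared test is the comparison of the primary outcome, the candidate list is fixed in advance, type I error barely moves, and a full protocol or analysis plan may put a number on the OR change. The first three points stand and limit the weight of the finding. The fourth does not remove it: the article states the selection rule itself, and a number would not stop the rule from selecting on the treatment estimate.

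A reader might infer more than the protocol supports:

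- *That the selection is done unblinded.* The Blinding section masks the statisticians. Masked labels do not hide how far the OR between two coded groups moves, so the dependence remains, but it is not an unblinded look.
- *That false interactions arise in about 37% of trials* (1 − 0.95⁹). That applies the general P<0.05 rule; the stated criterion for interaction is P<0.01.
- *That treatment itself could be removed for P≥0.05.* The second condition concerns the change in the treatment OR, which cannot be assessed for the treatment term. This reading is strained.
- *That all continuous covariates are cut into quartiles.* Only those failing linearity are; linear is the default.
- *That the benefit of adjustment is largely lost.* At 5% there was no power loss in either simulation. At 2% strong predictors were mostly kept.

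The simulated power figures in the table also need care. They set the conditional OR at 0.56, so the unadjusted effect (OR 0.63-0.64, power about 0.65) is weaker than the planned 49% vs 35%. They compare models and do not estimate the trial's power.

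**Conclusion.** The point holds for the adjusted OR and its confidence interval, and should be corrected. It does not touch the chi-squared comparison or the sample size. The rule selects covariates partly on chance imbalance, leaves out the factors the protocol regards as likely strong predictors, and reports an SE that ignores the selection.

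The clearest harm is that the adjusted result depends on an unstated threshold: at the design effect its significance differed from a fixed model's in 4-10% of simulated trials. Type I error inflation is small (0.051-0.062), and power loss runs from nil to about 3 points. A false treatment interaction has up to about an 8.6% chance if nine are tested independently; if retained, it would leave no overall adjusted effect to report. The retention, power and SE figures rest on assumed covariate effects and thresholds. With pure-noise covariates and a 5% threshold, the rule returned the unadjusted model in 98.8% of trials and did no harm.

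**What to change.** Replace the univariate screen, the backward removal and the change-in-OR rule with one adjusted model, written down before analysis:

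- treatment allocation, forced in;
- the stratification factors: parity, epidural and site;
- a short list of predictors known before randomisation, drawn from the protocol's own candidates, for example maternal age, body mass index, height, gestation and induction.

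Test treatment interactions one at a time, outside this model, and label them exploratory. Keep the chi-squared comparison and N = 416 as they are.

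The cost is a change of text and fewer programming steps. The one real loss is the freedom to change covariates after seeing the data. The Trial status section reports 128 participants recruited, and the protocol provides for amendments through the ethics committee, so the change can be made before analysis.

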#### Additional analyses

Subgroup analyses will be performed according to the technique of manual rotation employed (manual/whole hand versus digital/fingers) and according to operator ability (data will be divided into two approximately equal groups according to the success rate of the operator who performed the manual rotation).

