### Intervention

Manual rotation is performed at full dilatation (when the woman has the first urge to push or after one hour, whichever occurs first) if the fetal position is OT. The technique employed will be at the discretion of the operator performing the procedure. The intervention will be performed by obstetricians or midwives who are experienced in performing a manual rotation and have performed at least 20 procedures. All operators will complete a questionnaire outlining their technique and experience.

With the membranes ruptured, a vaginal examination is performed and the woman is asked to bear down. Constant pressure is exerted with the index finger against the lambdoid suture to rotate fetal head. This may take two to three contractions and the position is commonly held for two contractions while the woman bears down to reduce the risk of reverting back to the OP position. Alternatively, the examiner places two fingers behind the fetal ear or the entire hand behind the occiput and applies constant flexion and rotation to the fetal head.

For the purposes of the TURN-OUT Trial, the procedure will be described as a ‘digital rotation’ if only the fingers are used, and as a ‘manual rotation’ if the whole hand is used.

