### Comparator

Once full dilatation has been diagnosed (when the woman has the first urge to push or after one hour, whichever occurs first), women randomized to the sham rotation will have the same apparent vaginal examination as the intervention, but no rotational force will be applied. The woman is asked to bear down. The accoucheur places fingers in the vagina over five contractions as if they were performing a manual rotation.

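### Both planned subgroups are labelled with information that arises after randomisation: technique has no sham counterpart, and the ability label is set partly by the rotation arm's own results

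*Protocol article*

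**What the plan says.** The Additional analyses section names two subgroup analyses, "according to the technique of manual rotation employed (manual/whole hand versus digital/fingers) and according to operator ability". For the second, "data will be divided into two approximately equal groups according to the success rate of the operator who performed the manual rotation".

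Other sections show when these labels arise:

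- **Technique.** The Intervention section states: "The technique employed will be at the discretion of the operator performing the procedure". Under Randomization and allocation concealment, the randomisation call comes immediately before the procedure, so the technique used is known only after allocation.
- **Sham.** In the Comparator section, "no rotational force will be applied"; the only hand placement described is "The accoucheur places fingers in the vagina over five contractions as if they were performing a manual rotation".
- **Success.** The Discussion says operator success will be judged from fetal position on the ultrasound after the procedure in this trial. No other source of a success rate is described.
- **Operator.** Under Study conduct, the study investigator who confirms the position also randomises the woman, and the rotation or sham follows. An operator can therefore be identified for every woman in both arms.
- **Questionnaire.** "All operators will complete a questionnaire outlining their technique and experience" (Intervention).

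Randomisation is stratified by parity, hospital and epidural, not by operator or technique.

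**The concern.** A subgroup analysis of a treatment effect needs a label that is fixed independently of allocation and of what follows it, and that can be given to women in both arms. Technique used meets neither condition. If operators turn to the whole hand when the head is hard to move, a difference between techniques may simply show which cases were difficult.

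The ability label can be carried to both arms through the operator, but it is built from an intermediate result on the path to the primary outcome. An operator who happened to draw easier rotations is placed in the better half together with those women's good outcomes. The same operator's sham women had no part in setting the label. The article itself reports, under timing of the intervention, that failure to progress predicts inability to rotate, so success depends on the labour as well as on the operator.

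The Discussion raises operator experience as an issue for interpretation. A technique or skill effect that is partly an artefact could therefore be misread.

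**Working it through.** **Technique: no arithmetic needed.** Allocation comes first, the operator then chooses the technique, and sham women have none. Two comparisons remain: whole hand against fingers within the rotation arm, or each technique against all sham women. Neither compares groups formed by randomisation.

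**Plan's own figure.** For 49% versus 35%, two-sided α = 0.05 and 80% power, with mean proportion 0.42:

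n = [1.96·√(2·0.42·0.58) + 0.8416·√(0.49·0.51 + 0.35·0.65)]² / 0.14² = 194 per arm.

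The continuity correction gives (194/4)·[1 + √(1 + 4/(194·0.14))]² ≈ 208. The stated 208 per arm is reproduced and is used below.

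**Ability split when all operators are equally skilled.** Inputs:

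- 208 rotation-arm women (Sample size).
- Operative delivery 31% if the head is rotated and 49% if not. These are the article's rates for occiput anterior and occiput transverse early in the second stage (Epidemiology), borrowed here as the link between success and outcome.
- A stronger link of 25% versus 65%. This is an assumption.
- Success rate s = 75% and K = 6, 10, 20 or 40 operators. Both are assumptions. Six hospitals are listed, each needing a 24-hour service, so 6 is a plausible low end.

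The two links agree with the planned 35% in the rotation arm: 0.75·31 + 0.25·49 = 35.5%, and 0.75·25 + 0.25·65 = 35.0%.

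With m = 208/K rotations per operator, observed success rates vary by chance with SD = √(s(1−s)/m). Cutting at the middle separates the two halves by about 2·√(2/π)·SD = 1.596·SD in observed success. Sham women show no such gap, so

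false difference in treatment effect ≈ (risk if not rotated − risk if rotated) × 1.596 × SD.

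For K = 20: m = 10.4, SD = √(0.1875/10.4) = 0.134 and the gap is 0.214. This gives 0.18·0.214 = 3.9 points, or 0.40·0.214 = 8.6 points.

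| Operators | Gap in success | 31%/49%: formula | 31%/49%: simulated (type I error) | 25%/65%: formula | 25%/65%: simulated (type I error) |
|---|---|---|---|---|---|
| 6 | 0.117 | 2.1 | about 2 (6%) | 4.7 | about 4 (8%) |
| 10 | 0.152 | 2.7 | about 2.5 (6%) | 6.1 | about 6 (9%) |
| 20 | 0.214 | 3.9 | about 3.7 (7%) | 8.6 | about 8 (13%) |
| 40 | 0.303 | 5.5 | about 5.4 (9%) | 12.1 | about 12 (24%) |

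Differences are in percentage points. The simulations used 4,000 trials per scenario with identical operators, a cut near half of the rotation-arm women, and the interaction tested on the risk-difference scale at 5%. The formula runs slightly high, mainly with few operators, because it treats the observed rates as a large normal sample. When success has no link with outcome, the simulated bias is about zero and the type I error about 5%.

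**The case against.** A reader might infer that both subgroups exist only in the rotation arm, so that neither yields a randomised comparison. The documents do not support this for ability. The operator is identifiable for rotation and sham alike, and rotation versus sham within an operator is randomised, though not stratified by operator. If ability really were defined in one arm only, no treatment interaction could be estimated at all.

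A reader might also infer that a false interaction is certain and large. Its size depends on the number of operators, the success rate and the strength of the link, and the article gives none of these for its operators. Under the 31%/49% link the bias is small beside the contrast's own sampling SD of about 9.7 points. At P < 0.01, the threshold the Analysis section sets for interactions in the logistic model, the false rejection rate is only about 1 to 2.5%. The article's 87%/24% contrast would give larger figures, but it describes position at birth rather than position after the procedure.

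A third inference, that uptake of the procedure hangs on these subgroups, also fails. The Background ties uptake to the overall absolute reduction in operative delivery.

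Finally, the article is condensed and does not say how sham women are classified or whether an interaction will be tested. That omission is not criticised here. What stands is that the article does fix both grouping variables, and that both arise after randomisation.

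**Conclusion.** The point holds in a limited form. The technique subgroup is a non-randomised comparison as defined. The ability subgroup rests on a randomised contrast but uses a label that tilts it towards a larger apparent effect in the better-rated half. With equally skilled operators and an assumed 75% success, the tilt is about 2 to 5 points (type I error about 5 to 9%) for 6 to 40 operators under the article's own contrast. Under the assumed stronger link it is about 4 to 12 points (8 to 24%). It grows with the number of operators and vanishes if success is unrelated to operative delivery. These are additional analyses and the intention-to-treat primary comparison is untouched, so this is a moderate improvement and not a condition for the trial's validity.

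**What to change.** - Define both subgroups by operator characteristics recorded independently of the trial's results: usual technique and prior experience from the operator questionnaire. Apply the label to the operator in both arms and test a treatment-by-subgroup interaction.
- Check the questionnaire first. The article does not say when it is completed, or that it records usual technique and experience before the trial. Use it only to the extent that it was completed before the operator's trial procedures. This matters for the 128 women already recruited.
- If it cannot serve for ability, a leave-one-out success rate, which omits each woman's own result, is a fallback. Fix the cut-point in advance: in a check simulation, a leave-one-out rate cut at the sample median tipped the bias the other way when operators were few.
- Report technique used and observed success only as descriptive, non-randomised data for the rotation arm.

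The cost is a wording change, made before the data are analysed. The downside is minor: experience is an imperfect proxy for ability, and every operator must already have done at least 20 procedures, which may narrow the range.
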